##### Assessment of ocular refractive power

Ocular refractive power will be measured by an auto refractometer (KR800, TOPCON, Japan) after cycloplegia with 0.5% Tropicamide.

The average sphere, cylinder, and axis will be recorded.

##### Assessment of IOP

IOP is measured by a non-contact tonometry (NT-510, Nidek, Japan). If the participants cannot be coordinated with NCT, an iCare HOME tonometer (TA022, Icare Oy, Finland) is available. If the level of IOP is higher than normal, a Goldmann applanation tonometry (AT900, Haag Streit, Switzerland) will be used for further confirmation.

##### Ocular biological measurement

Includes central corneal thickness, anterior chamber depth, and axial length, measured by IOL-Master (IOLmaster 700, Carl Zeiss Meditec, Germany).

##### Slit-lamp photography

A slit-lamp photography system (BQ900, Haag Streit, Switzerland) will be used to capture retroillumination photos after dilation.

Standardized settings: magnification of × 10, beam height 4 mm, beam width 1 mm, flash off, illumination intensity 80%, and aperture 2.

##### Measurements of IOL position

IOL position (tilt and decentration) will be measured using CASIA2 or Pentacam connected to a digital Scheimpflug rotational camera as previously described [21]. After pupil dilation, two images at slit angles of 90° and 180° will be taken, and 3-dimensional imaging of the IOL position will also be measured.

The anterior and posterior surfaces of the cornea and both IOLs will be marked in the digital image to determine the visual axis of the eye and the optical axis of the IOL.

The tilt of the optical axis of the IOL relative to the visual axis and the distance between the IOL vertex and the visual axis will be calculated using Image-Pro plus 6.0 ([name], USA).

##### Cornea endothelium count

A noncontact specular microscope (NSP-9900, Konan Medical Inc., Japan) will be used to measure corneal endothelial cell density.

##### Fundus photography

Images centered on the disc and macula will be taken for each eye using fundus cameras (Nonmyd WX3D, KOWA, Japan; TRCNW400, TOPCON, Japan) after dilation.

Optic disc progression will be assessed by comparing the stereo photographs taken at baseline and the stereo photographs obtained at the follow-up examination and is defined by any of the following: (1) enlargement of vertical cup-to-disc ratio (VCDR), (2) neuroretinal rim notching (incidence or enlargement), (3) wedge-shaped RNFL defects (incidence or enlargement), or (4) disc hemorrhage, if not related to myopic changes.

##### Optical coherence tomography

Both a swept-source OCT (DRI-OCT Triton, TOPCON, Japan) and a spectral domain OCT (Cirrus 5000 HDOCT, Carl Zeiss Meditec, USA) devices will be used after dilation.

Image quality should be higher than 60 and 5 in DRI-OCT triton and Cirrus 5000 HD-OCT, respectively.

### Data management

#### Case report forms (CRFs)

The clinical coordinator will use paper CRFs for data collection. Eligible patients enrolled in the study will have individual patient CRF binders. The baseline CRFs should be completed on the first visit, signed by the investigator, and stored in the patient’s CRF binder. Investigators are required to complete CRFs at each visit for all enrolled participants after the completion of the research.

#### Data input and verification

The form data will be recorded and keyed into the EDC system and managed by data managers after data monitoring. The EDC system is secured digitally by investigators, and the study team will have access to the research data. If the data managers have questions about the data, investigators are required to respond to these questions on time, and the data managers will be allowed to verify and modify the ultimate data.

#### Data locking

The confirmed dataset will be locked by the principal investigator, monitor, and statistician for statistical analysis. The verified data cannot be modified unless problems arise after data locking, and investigators could modify data appropriately and record it after confirmation.

### Statistical analysis

#### Statistical methods

The normality of continuous data is to be checked using the Shapiro–Wilk test and histogram. Continuous data are to be summarized as the mean ± standard deviation, median, or interquantile range (IQR). Analysis of the primary and secondary outcomes is to be based on the intention-to-treat (ITT) and per-protocol (PP) analyses, and missing data will be imputed by multiple imputation or other appropriate methods. In the ITT analysis, participants are evaluated on the basis of the group to which they were randomly assigned, regardless of whether they actually received the surgery. In the PP analysis, participants are evaluated on the basis of the group to which they actually received the surgery to truly reflect the difference between the two groups. Paired *t* test will be used to compare pre- vs. postoperative visual acuity (in logMAR), spherical equivalent aberration, IOL tilt, and decentration at each time point after surgery. Comparison between the two treatment groups will be performed using a mixed model for continuous outcomes and a generalized estimated equation (GEE) model for categorical outcomes. The incidence of glaucoma-related AEs (primary outcome) by 1 year will be compared using the *χ*^2^ test or Fisher’s exact test. Kaplan–Meier survival curves are to be constructed to show the cumulative probability of glaucoma-related AEs over time in each group, and the log-rank test is used to compare the time to incidence of glaucoma-related AEs between the two study groups. Unadjusted and adjusted hazard ratio (HR) of glaucoma-related AEs and 95% CIs will be estimated by univariable and multivariable Cox proportional hazards model, respectively. Study group, stratification variable (laterality), and other baseline variables with *P* < 0.20 in the univariable analysis will be included in the multivariable model. The inter-eye correlation will be adjusted for all analyses including both eyes from the same subject.

A two-sided *p* < 0.0054 for interim analysis and *p* < 0.0492 for the primary analysis is considered to be statistically significant. All statistical analysis will be performed using Stata 16 (StataCorp, College Station, TX, USA) and other appropriate software.

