## Introduction

### Background

Treatment of pediatric cataract, one of the leading causes of childhood blindness globally, remains challenging because of the extremely high incidence of postoperative adverse events (AEs) [1–4]. Especially, the AEs related to the locations of secondary implanted IOL, such as iris-related inflammation, glaucoma-related AEs, and IOL positional stability potentially affect patients’ prognosis [5–9].

Theoretically, in-the-bag implantation of IOL prevents contact with the iris and may reduce the risk of AEs [10, 11]. However, due to the difficulties in performing secondary in-the-bag implantation in pediatric aphakic eyes, secondary IOL implantation with ciliary sulcus fixation in these patients is considered acceptable [12–15].

We and other investigators have demonstrated high feasibility of secondary in-the-bag IOL implantation in pediatric aphakic eyes [1, 7, 16–19]. In our prospective comparative study of 355 pediatric eyes undergoing secondary IOL implantation, we investigated the 3-year outcomes of these two methods and found that compared to ciliary sulcus secondary IOL implantation, in-the-bag IOL implantation reduced AEs and yielded better IOL centration and best corrected visual acuity (BCVA) for pediatric aphakia [1]. However, there have been no large, prospective cohort studies adjusting for important determinants of AEs and comparing outcomes of in-the-bag versus ciliary-sulcus secondary IOL implantation.

Whether or how much secondary in-the-bag IOL implantation benefits the pediatric patients more than sulcus implantation and deserves to be performed routinely by surgeons remains to be elucidated.

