### Sample size

According to the Zhongshan Ophthalmic Center’s outpatient record system, (1) the one-year incidence of glaucoma-related AEs in sulcus implantation is 12%. Assuming the in-the-bag implantation would reduce the absolute incidence to 0.7%, to achieve 90% power with a two-sided alpha of 0.0492 (the interim analysis at 6 months postoperatively spending alpha of 0.0054 by O’Brien-Fleming approach), 114 eyes are needed for each group (total of 228 eyes) using Fisher’s exact test with pooled variance. Allowing for a 20% loss to follow-up, 143 eyes should be needed in each group. Assumptions: % of bilateral = 75%, inter-eye correlation among bilateral patients = 0.5. For bilateral patients, two eyes have the same type of surgery. The number of patients (*X*) per group can be calculated by solving the following equation: *X* × 0.75 × 2/(1 + 0.5) + *X* × 0.25 = 143, *X* = 114 patients per group, a total of 228 patients. The sample size is calculated by PASS 16.0 (NCSS, LLC, USA). (2) IOL decentration in 3-dimension in the capsular group is 0.38 mm while in the sulcus group, it is 0.56 mm. Group sample sizes of 106 and 106 achieve 90% power to detect the mean difference of 0.18 between two trial arms with a common standard deviation for both groups of 0.40 and with a two-sided alpha of 0.0492 using a two-sided two-sample equal-variance *t*-test (same interim analysis as above for the 1-year incidence of glaucoma-related AEs). Allowing for a 20% loss to follow-up, 133 eyes should be needed in each group. Assumptions: % of bilateral = 75%, inter-eye correlation among bilateral patients = 0.5. For bilateral patients, two eyes have the same type of surgery. The number of patients (*X*) per group can be calculated by solving the following equation: *X* × 0.75 × 2/(1 + 0.5) + *X* × 0.25 = 133, *X* = 106 patients per group, a total of 212 patients. The sample size is calculated by PASS 16.0.

Considering the sample size calculated by the two primary outcomes, the largest one is selected: 114 patients per group, a total of 228 patients.

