### Randomization

Stratified block randomization will be applied for this trial. The eligible participants stratified by site who consented will then be divided into two strata according to secondary intraocular lens implantation in the unilateral eyes or bilateral eyes. Participants in each stratum will be randomized (1:1) to receive the assigned treatment from either secondary in-the-bag IOL implantation or secondary sulcus IOL implantation. An independent statistician without involvement in the study will generate the randomization sequence for each stratum using an online randomization number generator (http://www.randomization.com).Study participants with one study eye will be randomly assigned to one of the treatment groups.Study participants with two study eyes (both eyes are eligible):If capsular surgery is applicable for both eyes, study participants will be randomly assigned to one of the treatment groups, and both eyes will receive the same treatment.If capsular surgery is applicable for only one eye, which will be randomly assigned to one of the treatment groups, the contralateral eye will receive sulcus surgery or other appropriate treatment.

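### The analysis called per-protocol groups children by the surgery received, so it is as-treated and can favour the capsular arm; separately, the fellow-eye rule in Randomization conflicts with the same-treatment rule

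*Protocol article*

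**What the plan says.** **Analysis sets (Protocol article, Statistical methods).** Two analyses are named for the same outcomes: "Analysis of the primary and secondary outcomes is to be based on the intention-to-treat (ITT) and per-protocol (PP) analyses". Under ITT, "participants are evaluated on the basis of the group to which they were randomly assigned", whether or not they had that surgery. For the other, "In the PP analysis, participants are evaluated on the basis of the group to which they actually received the surgery"; the text adds that this shows the true difference between the groups. The two are not ranked there. Only the interim analysis is tied to the ITT population (Interim analyses).

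**Why crossover is conceivable.** Background explains that sulcus fixation is considered acceptable "due to the difficulties in performing secondary in-the-bag implantation in pediatric aphakic eyes". The next paragraph of the same section reports high feasibility of in-the-bag implantation.

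**Fellow eyes (Randomization).** The rule sits under the heading "Study participants with two study eyes (both eyes are eligible". Its second branch reads: "If capsular surgery is applicable for only one eye, which will be randomly assigned to one of the treatment groups", and then "the contralateral eye will receive sulcus surgery or other appropriate treatment". Sample size, by contrast, assumes: "For bilateral patients, two eyes have the same type of surgery". The Abstract and the trial design section also say that participants with two eligible eyes receive the same treatment in both.

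**The concern.** A per-protocol analysis restricts the data to those treated as assigned and leaves them in their randomised group. The rule here instead moves anyone who received the other procedure into the other group. That gives up the protection of randomisation, and the protocol's remark about showing the true difference claims the opposite.

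The likely direction is one-way. The capsular procedure requires the bag to be re-established during surgery, and the fallback described in Background is the sulcus. If the eyes in which this fails are anatomically worse, they leave the capsular group and join the sulcus group, and the capsular results improve for reasons unrelated to lens position. Both primary outcomes, decentration and glaucoma-related events at 1 year, are exposed.

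The fellow-eye rule is a separate fault. An eye that the heading calls eligible gets no random assignment and may receive sulcus surgery. If it were counted as a study eye, it would have no randomised group of its own.

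**Working it through.** **1. The plan's own figures reproduce.** For 12% v 0.7%, alpha 0.0492 and 90% power, the continuity-corrected normal approximation gives 114 eyes per group. Then 114/0.8 = 142.5, rounded up to 143, and X = 143/(0.75 × 2/1.5 + 0.25) = 143/1.25 = 114.4 patients. For decentration (0.18 mm, SD 0.40), 106 per group gives t-test power of 0.902; 106/0.8 = 132.5, rounded up to 133; and 133/1.25 = 106.4. The sample size is not in dispute here.

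**2. Model for the received-surgery analysis.**
- From Sample size: SD 0.40 mm, alpha 0.0492 (critical value 1.967), 114 evaluable eyes per group (treated as independent), 12% event rate.
- Assumed, not in the documents: lens position has no effect; a share h = 5% or 10% of eyes in each arm cannot take a bag lens; all such eyes assigned to the capsular group receive a sulcus lens; these eyes are 0.2 or 0.4 mm more decentred, or carry 2 or 3 times the glaucoma risk, with the overall risk held at 12%.

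After regrouping, the capsular group has 114(1 − h) eyes, none of them difficult. The sulcus group has 114(1 + h), of which 2h × 114 are difficult.

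**3. Decentration.** False difference D = [2h/(1 + h)] × d. Standard error = 0.40 × √(1/n_C + 1/n_S), about 0.053 mm. Rejection is two-sided, normal approximation.

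| h | d (mm) | D (mm) | D/SE | Rejection |
|---|---|---|---|---|
| 5% | 0.2 | 0.019 | 0.36 | 6.4% |
| 5% | 0.4 | 0.038 | 0.72 | 11.0% |
| 10% | 0.2 | 0.036 | 0.68 | 10.4% |
| 10% | 0.4 | 0.073 | 1.37 | 27.4% |

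Against the planned 0.18 mm, D runs from 0.019/0.18 = 11% to 0.073/0.18 = 40%.

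**4. Glaucoma-related events.** With risk ratio r, the risk in other eyes is p = 0.12/(1 − h + hr), which is also the capsular rate. The sulcus rate is [(1 − h)p + 2h·rp]/(1 + h). Fisher rejection is by exact enumeration with rounded group sizes (108 v 120; 103 v 125). The χ² column is the normal approximation with pooled variance under the null.

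| h | r | Capsular | Sulcus | Difference (points) | Fisher | χ² |
|---|---|---|---|---|---|---|
| 5% | 2 | 11.4% | 12.5% | 1.1 | 4.3% | 5.6% |
| 5% | 3 | 10.9% | 13.0% | 2.1 | 5.8% | 7.5% |
| 10% | 2 | 10.9% | 12.9% | 2.0 | 5.7% | 7.2% |
| 10% | 3 | 10.0% | 13.6% | 3.6 | 10.7% | 12.9% |

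**5. Reference points.** Grouped as randomised, the expected difference is 0 and Fisher rejects in 2.9% of trials (114 v 114, 12% in both). With r = 1 the regrouped rates are 12% v 12% and the bias is zero; Fisher then rejects in 3.8-3.9%. So 4.3% is above Fisher's own level in this setting but not above the nominal 4.92%.

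**6. Fellow eyes.** Side by side: both eyes are called eligible; one is randomised and the other is not; elsewhere, two eligible eyes have the same surgery. A child whose randomised eye goes to the capsular group and whose other eye gets a sulcus lens satisfies the Randomization branch and violates the statements in the Abstract, the trial design section and Sample size. The documents do not say that the non-randomised eye is analysed, so no size is attached to this part.

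**The case against.** The strongest reply is that ITT is also planned and correctly defined, so crossover leaves it intact and only the second analysis is affected. That stands. Ranking the two analyses may also be left to a statistical analysis plan that is not shown, so silence on which one decides is not the defect. The defect is the definition, which is stated and wrong, together with the claim made for it.

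It can also be said that crossover may be rare. Background reports high feasibility, the inclusion criteria require sufficient anterior segment space and a volumized Soemmerring's ring, and for two-eye participants Randomization makes assignment depend on whether capsular surgery is applicable. No section gives a crossover rate or says that such eyes do worse, and a 0.4 mm penalty is one full SD. This stands too, and it is why the figures above are illustrations over a range.

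Two stronger readings are tempting. A reader might infer that difficult eyes will in fact be moved and will create a capsular benefit. The documents support only that they could be, in this one analysis, if the eyes exist and do worse. A reader might also infer that non-randomised fellow eyes enter the comparison and contaminate ITT as well. No section says that they are analysed. Such an eye might fail the ring criterion, in which case the heading that calls both eyes eligible would be the drafting error.

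**Conclusion.** The point holds in a limited form. The analysis labelled per-protocol is as-treated, and the claim that it shows the true difference is not justified. Whether and how far it is biased depends on two quantities that the documents do not give: how many capsular-assigned eyes receive a sulcus lens, and how much worse those eyes do. Over the assumed ranges, with no true effect, the false capsular advantage is about 0.02-0.07 mm in decentration (about 6-27% false positives) and about 1-3.6 points in glaucoma-related events (about 4-13%, depending on the test). It is zero without excess risk, and ITT is not affected by this mechanism.

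The contradiction over fellow eyes is certain as a matter of text. Its effect on any analysis is conditional on those eyes being counted.

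**What to change.** 1. Base the primary conclusion on ITT.
2. Define per-protocol as eyes that received the assigned procedure, analysed in their randomised group, and make it supportive. Some selection remains in such a set, which is a further reason for ITT to decide.
3. Label any grouping by surgery received as an exploratory as-treated analysis, and delete the wording that says it shows the true difference.
4. State that fellow eyes which were not randomised are excluded from all between-group comparisons.
5. Reconcile the Abstract, the trial design section, Sample size and Randomization on eligible fellow eyes. This review takes no view on which surgery such an eye should receive.

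Items 1-3 are changes of wording. Item 4 costs a few non-randomised eyes, which had no randomised comparison to contribute. Children already randomised should stay in their strata: Trial status reports the first randomisation on December 14, 2021, and nothing here requires re-stratifying.

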### Objectives

#### Main objective

The main objective is to compare the safety of in-the-bag versus ciliary-sulcus secondary intraocular lens (IOL) implantation in pediatric aphakia, including IOL decentration and the incidence of glaucoma-related adverse events.

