#### Secondary outcomes

The secondary outcomes include the following:Incidence of glaucoma-related AEs by 6 months, 3 years, 5 years, and 10 years postoperativelyIOL decentration by 6 months, 3 years, 5 years, and 10 years postoperatively.Incidence of other AEs by 6 months, 1 year, 3 years, 5 years, and 10 years postoperatively. Other AEs include IOL dislocation, iris synechia, corectopia and/or discoria, visual axis opacification, corneal endothelium decompensation, and retinal detachment. It will be recorded separately using criteria previously reported [22, 23].IOL tilt by 6 months, 1 year, 3 years, 5 years, and 10 years postoperatively.VA and ocular refractive power by 6 months, 1 year, 3 years, 5 years, and 10 years postoperatively.

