#### Testing procedures

##### Assessment of visual acuity

Visual acuity will be evaluated with an Early Treatment Diabetic Retinopathy Study (ETDRS) chart. For those who are unable to use the ETDRS chart, visual acuity is evaluated with Lea Symbol Chart or Teller Acuity Cards.

All decimal visual acuity outcomes will be converted to logarithm of the minimum angle of resolution (logMAR) units for the statistical analyses.

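### The pre- versus postoperative paired t test cannot be run for IOL tilt or decentration; for acuity and refraction it can, but it does not compare the arms and, run by eye, breaks the plan's inter-eye rule

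*Protocol article*

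**What the plan says.** Under Statistical methods, the article plans a paired t test, which "will be used to compare pre- vs. postoperative visual acuity (in logMAR), spherical equivalent aberration, IOL tilt, and decentration at each time point". The next sentence reads: "Comparison between the two treatment groups will be performed using a mixed model for continuous outcomes". Later in the same paragraph comes a general rule: "The inter-eye correlation will be adjusted for all analyses including both eyes from the same subject".

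The main objective is to "compare the safety of in-the-bag versus ciliary-sulcus secondary intraocular lens (IOL) implantation in pediatric aphakia", and the exclusion criteria rule out eyes that had a lens implanted at the first operation. Under Measurements of IOL position, the quantities calculated are "The tilt of the optical axis of the IOL relative to the visual axis and the distance between the IOL vertex and the visual axis".

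The outcome lists are postoperative. Decentration is a primary outcome at 1 year and a secondary outcome at the other time points. Tilt is listed as "IOL tilt by 6 months, 1 year, 3 years, 5 years, and 10 years postoperatively". Acuity and refraction are measured both at baseline and after surgery. For children who cannot use the ETDRS chart, "visual acuity is evaluated with Lea Symbol Chart or Teller Acuity Cards".

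**The concern.** One sentence treats four measures as if each had a value before and after surgery. Two of them, tilt and decentration, describe where an implanted lens sits, and these eyes have no implant until the trial operation. An analyst who followed the sentence literally could not comply for a primary outcome.

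The other two measures do have baseline values, but the test asks a question that the trial was not set up to answer. A change from before to after surgery combines several things:

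- the operation itself;
- visual development in children who may enter at 18 months and are followed for 10 years;
- for acuity, a possible move from one chart to another as the child grows;
- for refraction, the lens power, which is chosen in both arms to reach a target between +4 D and emmetropia.

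None of these separates the arms. Most children are also expected to contribute two eyes. A plain paired t test by eye treats those eyes as independent, so its p-values would be too small and could be read as stronger evidence than they are.

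**Working it through.** **1. Does a preoperative tilt or decentration exist?** Set side by side:

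- Population (Main objective, Exclusion criteria): aphakic eyes, with primary implantation excluded.
- Definition (Measurements of IOL position): tilt needs the optical axis of the IOL, and decentration needs its vertex.
- Time points (Outcomes): postoperative only.

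Table 1 schedules CASIA2 and Pentacam at the baseline visit, but there is no implant to image at that visit. The paired difference is undefined for both measures.

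**2. Does the decentration sample size depend on the paired test?** Inputs from Sample size: means 0.38 and 0.56 mm, difference 0.18, SD 0.40, two-sided alpha 0.0492, power 90%, two-sample t test.

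- Normal approximation: n = 2 × (z₁₋α/₂ + z₁₋β)² × (SD/difference)² = 105 per group.
- Noncentral t: power is 0.8995 at 105 and 0.9022 at 106, so 106 is the smallest n reaching 90%.
- Allowing for 20% loss: 106 / 0.80 = 132.5, rounded up to 133.

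The plan's 106 and 133 are reproduced. The calculation compares postoperative values between arms and uses no preoperative value, so removing the paired test leaves it unchanged.

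**3. What if the acuity and refraction tests are run by eye without adjustment?** Inputs from Sample size: 75% bilateral, inter-eye correlation 0.5. The plan does not tie that correlation to pre-post changes; applying it to them is an assumption.

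- Mean eyes per child: 0.75 × 2 + 0.25 × 1 = 1.75.
- Variance of a child's summed changes, in units of one eye's variance: 2 × (1 + 0.5) = 3 if bilateral and 1 if unilateral. The average is 0.75 × 3 + 0.25 × 1 = 2.50.
- Design effect for the mean over eyes: 2.50 / 1.75 = 1.4286.
- Standard error understated by √1.4286 = 1.195, about 1.20.
- Actual size of a nominal 5% test: 2 × [1 − Φ(1.96 / 1.195)] = 2 × [1 − Φ(1.64)] ≈ 0.10.

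**4. What would baseline adjustment add in the mixed model?** At a single visit, a baseline covariate with baseline-outcome correlation r multiplies the residual variance by 1 − r². The plan gives no r, so a range is assumed:

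- r = 0.3: 1 − 0.09 = 0.91, a reduction of 9%.
- r = 0.5: 1 − 0.25 = 0.75, a reduction of 25%.

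This applies to acuity and spherical equivalent only, because tilt and decentration have no baseline.

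**The case against.** The strongest reply is that the treatment comparison is already sound. A reader might infer that the paired tests take the place of a randomised comparison for acuity and refraction. The document does not support that: the sentence after the paired tests assigns the between-group comparison of continuous outcomes to a mixed model, and all four measures are continuous. The article does not even say whether the paired tests are done within each arm or over all eyes, and nowhere does it offer a pre-post change as evidence of efficacy. This part of the reply stands in full.

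A second reply is that the plan promises to adjust every two-eye analysis, so the 10% error rate describes an analysis that it says it will not run. That is fair as to the figure, which is conditional. It does not rescue the wording, because an ordinary paired t test on eyes has no term for that correlation. The named test and the stated rule cannot both be followed.

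A third inference would be that baseline acuity and refraction are left out of the mixed model. The article is silent on that model's covariates, and such detail is commonly left to the analysis plan. Silence does not show omission, so baseline adjustment is a recommendation here and not an error found.

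None of these replies touches tilt and decentration. That part is not silence: the text names a test that cannot be computed.

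**Conclusion.** The point holds in a limited form.

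- **Certain from the document alone:** the paired pre-post test of tilt and of decentration, a primary outcome, cannot be carried out.
- **Also established:** for acuity and spherical equivalent the test is feasible but does not address in-the-bag versus sulcus, and its ordinary eye-level form conflicts with the plan's inter-eye rule.
- **Conditional size:** a standard error too small by about 1.20 and an actual error rate of about 10%, if the test is run unadjusted and the planning correlation of 0.5 also holds for changes.
- **Possible gain:** 9% to 25% less residual variance from baseline adjustment, for assumed correlations of 0.3 to 0.5.

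The practical harm is modest. The between-arm analysis of these outcomes is already specified, and no sample size, alpha or power figure changes.

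**What to change.** Amend the Statistical methods wording in three places.

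1. Remove IOL tilt and decentration from the paired-test sentence. State that both are compared between arms on postoperative values with the mixed model already named.
2. If pre-post tests of acuity and spherical equivalent are kept, label them descriptive. Replace the plain paired t test with a version that accounts for two eyes per child, for example a model of the change with a random effect for child.
3. In the between-arm mixed model for logMAR acuity and spherical equivalent, name the baseline value as a covariate.

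The cost is wording only. Baseline acuity and refraction are already collected, and no visit, measurement or sample size is affected.

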**Methods:**

The study is a multicenter, single-blinded RCT with 10 years of follow-up. Overall, a minimum of 286 eyes (approximately 228 participants assuming 75% have two study eyes) will be recruited. This study will be carried out in four eye clinics across China. Consecutive eligible patients are randomized to undergo either secondary in-the-bag IOL implantation or secondary sulcus IOL implantation. Participants with two eyes eligible will receive the same treatment. The primary outcomes are IOL decentration and the incidence of glaucoma-related AEs. The secondary outcomes include the incidence of other AEs, IOL tilt, visual acuity, and ocular refractive power. Analysis of the primary and secondary outcomes is to be based on the intention-to-treat and per-protocol analysis. Statistical analyses will include the *χ*^2^ test or Fisher’s exact test for the primary outcome, mixed model and generalized estimated equation (GEE) model for the secondary outcome, Kaplan–Meier survival curves for the cumulative probability of glaucoma-related AEs over time in each group.

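### The test named for the primary glaucoma outcome does not, in standard form, make the inter-eye adjustment the same section promises; run as written on eyes, its type I error would be about 10% (chi-square) or 6.5–8% (Fisher) instead of 4.92%

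*Protocol article*

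**What the plan says.** Three statements in the Statistical methods section bear on the 1-year glaucoma outcome.

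- A general rule for comparing the groups: a mixed model for continuous outcomes and "a generalized estimated equation (GEE) model for categorical outcomes".
- A specific rule for this outcome: "The incidence of glaucoma-related AEs (primary outcome) by 1 year will be compared using the" chi-square test or Fisher's exact test.
- A general promise: "The inter-eye correlation will be adjusted for all analyses including both eyes from the same subject".

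The Methods part of the abstract gives chi-square or Fisher for the primary outcome and "mixed model and generalized estimated equation (GEE) model for the secondary outcome".

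The Sample size section counts eyes. It asks for 114 eyes per group by Fisher's exact test "to achieve 90% power with a two-sided alpha of 0.0492". It assumes 75% bilateral patients, the same surgery in both eyes and "inter-eye correlation among bilateral patients = 0.5". The Randomization section allocates the child when both eyes suit capsular surgery. When only one eye does, that eye alone is randomised.

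**The concern.** Most children are expected to contribute two eyes to the same arm, and outcomes in a child's two eyes are assumed to be correlated. A textbook chi-square or Fisher test on eyes counts each eye as a separate observation. It therefore understates the variance of the difference between arms and rejects too often under the null.

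The promise of adjustment shows that the authors know this. But the section names a test that does not adjust in its standard form, and it does not name an adjusted version. The abstract places GEE, which can handle the pairing, with the secondary outcome. One analyst could run an unadjusted Fisher test and another a clustered analysis; each could cite the protocol, and their p-values would differ. For a primary safety outcome tested at a fixed 4.92%, that choice should not be open once results are known.

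**Working it through.** **Inputs**, all from Sample size: rates 12% (sulcus) and 0.7% (capsular); two-sided alpha 0.0492; power 90%; loss 20%; 75% bilateral; correlation 0.5; 114 patients per group.

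**1. The plan's own figures reproduce.** The pooled-variance formula for two proportions is n = [z(α/2)·√(2p̄q̄) + z(β)·√(p₁q₁ + p₂q₂)]² / d², with p̄ = 0.0635 and d = 0.113:

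- (1.967 × 0.3449 + 1.2816 × 0.3355)² / 0.01277 = 96.2, so 97 eyes
- with continuity correction: (96.2/4) × (1 + √(1 + 4/(96.2 × 0.113)))² = 113.2, so **114 eyes**
- 114/0.8 = 142.5, so **143 eyes**
- X = 143 / (0.75 × 2/1.5 + 0.25) = 143/1.25 = 114.4, given as **114 patients**

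So the sample size allows for the correlation. The question is only whether the named test does.

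**2. Design effect of an unadjusted eye-level comparison.** A child contributes 0.25 × 1 + 0.75 × 2 = 1.75 eyes on average. The variance contribution is 0.25 + 0.75 × 2 × (1 + 0.5) = 2.5.

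- Design effect = 2.5/1.75 = **1.43**
- Standard error understated by a factor of √1.43 = 1.20

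**3. Type I error of unadjusted chi-square (large-sample formula).** 2 × [1 − Φ(1.967/1.195)] = **9.98%**.

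Other correlations, still at 75% bilateral:

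| Correlation | Type I error |
|---|---|
| 0.2 | 6.9% |
| 0.3 | 7.9% |
| 0.5 | 10.0% |
| 0.8 | 13.0% |

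The 10% is therefore not an upper bound.

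**4. Exact enumeration at correlation 0.5.** The common null rate is taken as 6.35% (the mean of the two planned rates) or 12%.

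| Children (eyes) per arm | Null rate | Chi-square | Fisher |
|---|---|---|---|
| 114 (200) | 6.35% | 9.8% | 7.1% |
| 114 (200) | 12% | 10.0% | 7.8% |
| 91 (159), after 20% loss | 6.35% | 9.9% | 6.6% |
| 91 (159), after 20% loss | 12% | 10.2% | 7.4% |

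Fisher's inflation is smaller because the test is conservative to begin with: with independent eyes its actual error in these settings is 2.8–3.5%.

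**5. Interim.** If the interim analysis used the same unadjusted chi-square, the formula at nominal 0.0054 gives about 2.0%.

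**6. A clustered chi-square does hold its level.** A score-type chi-square with patient-clustered variance was simulated at correlation 0.5, null rates 6.35% and 12%, and 91 or 114 children per arm. Type I error was 4.7–4.9%. Power for 12% versus 0.7% with 91 children per arm was 98%, although about 42% of those replicates had no capsular event.

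**7. Chance of no events in the capsular arm at 0.7%.** With independent eyes this is 0.993 raised to the number of eyes. With correlation 0.5, a bilateral child has no event in either eye with probability 1 − (0.003525 + 0.006951) = 0.98952.

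| Children per arm | Independent eyes | Correlation 0.5 |
|---|---|---|
| 114 (86 bilateral, 28 unilateral) | 0.993²⁰⁰ = 25% | 0.98952⁸⁶ × 0.993²⁸ = 33% |
| 91 (68 bilateral, 23 unilateral) | 0.993¹⁵⁹ = 33% | 0.98952⁶⁸ × 0.993²³ = 42% |

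With an empty arm, an ordinary odds ratio or hazard ratio has no finite estimate.

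**The case against.** The strongest reply is that the protocol already commits to adjusting for inter-eye correlation wherever both eyes are used, and that a chi-square test can be adjusted: Rao-Scott and robust score versions are standard. On that reading the named test and the promise coexist, and the mechanics belong in the analysis plan.

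Much of this stands. A reader might infer that the trial's false-positive rate is 10%, or that the plan ignores the pairing. The documents support neither. The sample size allows for the correlation, the adjustment is promised, and the inflation arises only if that promise is not carried into the primary test. A reader might also infer that confidence intervals will be too narrow, but the section attaches no interval to the chi-square or Fisher test. Nor is 10% a common figure for both tests, since Fisher's is lower.

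Two further limits apply. The Statistical methods section does not state the unit of the primary test; eyes is inferred from the Sample size section. And the same-surgery rule has the stated exception for children with only one eye suited to capsular surgery.

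The reply does not remove the problem. The section offers Fisher as an equal alternative, and Fisher has no standard adjusted form. An adjusted chi-square is nowhere named. This is not a detail merely left for later: the article does fix the primary test, and in its standard form that test conflicts with another sentence of the same section.

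**Conclusion.** The point holds as an internal contradiction with a conditional consequence. The Statistical methods section names a primary test whose standard forms do not make the adjustment it promises. If that test is run as written on eyes, type I error is about 10% (chi-square) or about 6.5–8% (Fisher) instead of 4.92%. If the promise is honoured with a properly clustered test, error stays near nominal.

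The size rests on 75% bilateral children, both eyes in the same arm, correlation 0.5, and null event rates between 6.35% and 12%. A weaker correlation reduces the inflation and a stronger one increases it. Because this is a primary safety outcome and the text permits both readings, it should be settled before outcomes are compared by arm.

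**What to change.** In the Statistical methods section and the matching summary in the abstract, replace the choice between chi-square and Fisher with one named test that treats the child as the randomised unit. Either of these would do:

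- a patient-clustered chi-square (Rao-Scott or robust score form), which is the smaller change; or
- a permutation test of the difference in eye-level event proportions, permuting children within the randomisation strata (site by laterality).

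Report the risk difference with a patient-clustered interval. Keep GEE and Cox as supportive analyses, since the chance of an empty capsular arm at the assumed 0.7% is about 25–42%, depending on loss to follow-up and correlation. Use the same test at the interim.

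The cost is a sentence or two of text, a short program, and a slightly less favourable p-value than the unadjusted test would give. Power with the clustered chi-square is about 98% at 91 children per arm. A permutation test stratified by laterality alone gave about 97% power and a somewhat conservative type I error of 3.5–3.9%. Stratifying by site as well has not been checked and should be simulated before that option is chosen.
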